## Abstract

**Background:**

Breast cancer patients and their families are under various pressures in the process of disease diagnosis and treatment, which seriously threaten their physical and mental health. Findings from existing research suggest that good family resilience can help breast cancer families better adapt and cope with adversity and challenges. However, there are only a few intervention studies on family resilience and no intervention studies on resilience among the families of breast cancer patients. Therefore, this study aims to explore appropriate measures to improve the resilience level of breast cancer families and help them better cope with the disease.

**Objective:**

The purpose of this study protocol is to demonstrate a coping-focused family resilience intervention to increase the level of resilience in the families of breast cancer patients and help them better cope with adversity.

**Methods:**

The trial will recruit 80 breast cancer families and randomly assign them to experimental and control groups in a 1:1 ratio. The control group will receive routine care, and the intervention group will receive a 6-week one-on-one online family resilience intervention based on the control group. Two groups of subjects will be assessed at baseline and at 1 week, 1 month, and 3 months after the intervention. The primary outcome is family resilience, and the secondary outcomes are coping style, social support, family disease burden, and levels of anxiety and depression.

**Expected results:**

We hypothesized that after the intervention, the intervention group would have significantly higher levels of family resilience than the preintervention and control groups. In the intervention group, other aspects related to family resilience, such as family disease burden and anxiety and depression levels of patients and their families, were significantly alleviated, and disease coping and social support levels were improved accordingly.

**Discussion:**

If the program works, it can help breast cancer families identify family strengths and resources to proactively address challenges so that families can successfully navigate the crisis and patient and family recovery can be facilitated. It can also provide a practical path for clinical workers to help breast cancer families adjust rationally.

**Clinical Trial Registration:**

This study has been registered in the Chinese Clinical Trials Registry (Registration Number: http://www.chictr.org.cn/ChiCTR2100052108).

## Introduction

According to Global Cancer Statistics (GLOBOCAN), there were approximately 2.3 million new cases of breast cancer worldwide in 2020, ranking the disease first among all types of cancer (Sung et al., 2021). Global Cancer Survival Data (CONCORD-3) shows a continued increase in the 5-year net survival rate for breast cancer (Allemani et al., 2018). The 5-year net survival rate of Chinese breast cancer patients is up to 84% (Zeng et al., 2018), and the age of onset tends to be younger (Chen et al., 2018). With the increasing incidence of breast cancer, the improvement of survival rates, and the younger age of onset, people are paying increasing attention to the quality of life of breast cancer patients.

The diagnosis and treatment of breast cancer not only causes great distress to the patient physically, psychologically and socially but induces many physical, psychological and social problems for family members (Wagner et al., 2006; Rabin et al., 2009; Yu and Sherman, 2015; Feeney et al., 2018; Tsaras et al., 2018; Boamah et al., 2021). A series of problems faced by patients and their families often lead to unbalanced family relationships and reduced family intimacy and function that challenges patients and their families (Chen, 2015). It easily causes a family crisis and affects the patient’s recovery and quality of life. In China, the incidence of breast cancer has been increasing annually in recent years, and the incidence of breast cancer combined with depression has shown a significant upward trend (Su, 2021; Sung et al., 2021). The diagnosis and treatment of breast cancer has placed a heavy burden on family members, and the marital quality of breast cancer patients has also been seriously damaged (Pan et al., 2022; Wu et al., 2022).

Meanwhile, when faced with the severe challenges of breast cancer, some families are able to adapt effectively and make positive changes that allow them to recover and grow (Markman et al., 2020). Research shows that family resilience plays an important role. Family resilience is an important protective factor for individual resilience (Zhang, 2015), which can directly or indirectly improve individual resilience, patients’ quality of life and disease coping ability, and patients’ subjective well-being and mental health (Chen et al., 2019). During the formation and development of family resilience, breast cancer families have experienced positive changes in disease cognition, member psychology, family atmosphere, and family relationships (Wu, 2020). However, research on breast cancer family resilience has mostly focused on the relationship between related factors, and no further interventions to improve family resilience have been reported. Therefore, it is important to design effective interventions to increase the level of resilience among the families of breast cancer patients in China.

Family resilience was first proposed by Walsh based on the concept of psychological resilience, which elevates resilience from the individual level to the family level (Walsh, 2003). Dai Yan believes that family resilience is not only a trait and ability to help families adjust and adapt under pressure and adversity but also a process of helping the entire family dynamically adjust to better adapt and cope with adversity and changes (Dai, 2008).

At present, family resilience has attracted increasing attention from scholars worldwide, and intervention research on family resilience is still in its infancy. From a previous literature review, only nine family resilience intervention studies have entered clinical trials (Weine et al., 2003; Chartier et al., 2010; Lim and Han, 2013; Inci and Temel, 2016; Miran, 2016; Dorell et al., 2017; Wang, 2017; Faarup et al., 2019; Yu et al., 2020), of which only three are randomized controlled studies (Inci and Temel, 2016; Wang, 2017; Yu et al., 2020), and there is no report on family resilience intervention studies for breast cancer patients. Most family resilience intervention studies are in the construction or preexperimental stage of the intervention plan (Riley et al., 2008; Foster et al., 2012; Lim and Han, 2013; Miran, 2016; Zhao, 2016; Dorell et al., 2017). The construction process and content of the intervention programs have not been reported in detail. Current research on family resilience interventions often uses multifamily group meetings involving patients and family members from multiple families (Weine et al., 2003; Lim and Han, 2013; Inci and Temel, 2016). The meetings mainly focus on disease knowledge, stress and emotion management, coping with family problems, and family communication methods. Some studies focus on family communication interventions (Dorell et al., 2017; Faarup et al., 2019). Although the findings suggest that most interventions had some effect on improving the study subjects’ family resilience levels and reducing related psychosocial problems, the format of multifamily group meetings may not be effective in China.

Due to the influence of traditional Chinese culture and the introverted nature of Chinese people, people are not used to expressing their feelings and sharing family problems publicly. This is consistent with what we learned earlier. Patients and their families prefer one-on-one family meetings. Therefore, one-on-one family meetings may be more effective than multifamily group meetings. Meanwhile, the postoperative treatment and follow-up of patients are mostly performed in local hospitals or outpatient clinics, and there is no time to participate in an intervention. In addition, repeatedly making appointments for patients and their families to come to the hospital to participate in an intervention increases the burden on the family and the risk of contracting COVID-19. Therefore, online meetings can solve these problems very well. The online meeting time and location are more flexible. Participants only need to find a relatively quiet place to join the meeting. The meeting time can also be adjusted if participants require it. Additionally, online meetings can be recorded. If some participants are absent due to personal reasons, they can learn about the content of the meeting from the video. Online meetings greatly improved the implementability and convenience of intervention programs.

Among the current family resilience intervention research, some studies are based on family resilience theory (Lim and Han, 2013; Inci and Temel, 2016; Miran, 2016), and some studies are based on other related theories (Chartier et al., 2010; Dorell et al., 2017; Wang, 2017; Faarup et al., 2019; Yu et al., 2020). Different theoretical foundations have different intervention programs, and the intervention effects also have certain differences. To this end, our research group [name] used grounded theory to study the formation process of family resilience of breast cancer patients, modeled the family resilience process of resilience among the families of breast cancer patients, and laid a theoretical foundation for formulating a breast cancer family resilience intervention program (Wu, 2020).

[name]′s family resilience process model of breast cancer patients describes the attitudes, strategies and influencing factors of Chinese families coping with a family member’s breast cancer (Wu, 2020). The process model shows that the formation of family resilience is affected by multiple protective factors, of which the coping process is the core category of the family resilience process model. The coping process dynamically modulates changes in disease perception and family resilience outcomes during the family resilience process and plays a leading role in the formation and development of family resilience. The coping process is also a game process of various facilitating and hindering factors, helping families to better adjust, adapt and cope with adversity and changes. Therefore, the coping process becomes the core and focus of family resilience interventions.

Walsh’s family resilience framework places the family at the core of a unit, emphasizing that family resilience is the result of the interaction of individuals, families and societies (Walsh, 2003). The theory divides the core of family resilience into three key processes: belief systems, organizational patterns, and communication/problem-solving processes. Many key elements of these three processes, such as meaning making, flexibility, and open emotional expression, can be intervened. The model has a relatively simple structure and is easy to operate, which is more suitable for clinicians assessing and intervening in patients’ family conditions, and it provides a more concise and easy-to-operate strategy and framework for family resilience intervention. Therefore, we should focus on the coping process in [name]′s family resilience process model of breast cancer patients and use Walsh’s family resilience theory as a framework to construct a family resilience intervention plan for families of breast cancer patients in the Chinese context.

This intervention plan was based on relevant theories and combined with literature research to form the first draft of the family resilience intervention plan for Chinese breast cancer patients. Qualitative interviews were then conducted with breast cancer patients and their families, doctors and nurses in relevant departments. According to their comments, the content of the intervention plan was adjusted, and a revised draft of the intervention plan was formed. Experts in relevant fields were then contacted *via* email for two rounds of expert consultation on the content of the intervention program. According to the opinions of experts, the content of the intervention plan was adjusted for the second time, and the final draft of the family resilience intervention plan for breast cancer patients was formed. Finally, the intervention program is put into clinical practice for large-scale randomized controlled trials.

This study aimed at the family crisis of breast cancer patients and based on rigorous evidence, a coping-focused family resilience intervention program (CFFRI) for Chinese breast cancer patients will be validated. If the intervention proves effective, it could be used to increase the family resilience of breast cancer patients and help them better cope with crises and challenges.

### Hypotheses

The research hypotheses are as follows:

After the intervention, the family resilience level of the intervention group will be significantly improved compared with that before the intervention.After the intervention, the family resilience level of the intervention group will be significantly improved compared with that of the control group.After the intervention, other aspects related to family resilience in the intervention group, such as the family disease burden and anxiety and depression levels of patients and their families, will be significantly relieved, and the level of disease coping and social support will be improved accordingly.

## Materials and methods

### Study design

Due to the nature of the experiment, the interventionists could not be blinded in this study, so this study used a single-blind randomized controlled trial. Subjects will be included in the study in strict accordance with the inclusion and exclusion criteria. Eligible patients and their families will be included in the study according to their wishes. Participating families will be randomly divided into a control group and an experimental group according to computer-generated random numbers, with a distribution ratio of 1:1 (Figure 1). The control group will receive usual care. The experimental group will receive a family resilience intervention on the basis of usual care that will blind participants, recruiters and data collectors. This study constructs a family resilience intervention plan for breast cancer patients in strict accordance with the SPIRIT 2013 and CONSORT 2010 statement (Chan et al., 2013; Eldridge et al., 2016).

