### Randomization

Eighty random numbers will be generated by a computer and randomly divided into an intervention group and a control group with a distribution ratio of 1:1. The assigned numbers will be sealed in 80 opaque envelopes. Recruiters will enroll research subjects who meet the research conditions, agree to participate in the research, and sign an informed consent form. Subjects will randomly draw envelopes, enter their assigned groups, and have baseline measurements taken. Participant recruitment and assignment will be done by two independent researchers, blinding participants, recruiters and data collectors.

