### Intervention

#### Control group

Families in the control group will receive usual care. Usual care includes the following: First, the issuance of health handbooks, which include breast cancer-related knowledge, postoperative rehabilitation exercise guidance, clinical nursing practice guidelines for preventive behavior of breast cancer-related lymphedema and a breast cancer postoperative follow-up checklist. Second, a WeChat group will be established where researchers answer questions and share disease-related knowledge with participants. Finally, Everyone will be encouraged to share positive experiences related to the disease in the WeChat group to encourage and support each other.

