#### Experimental group

The experimental group will implement one-on-one online family resilience intervention on the basis of usual care. Intervention implementation will be led by a professionally trained nursing graduate student and a breast cancer-related unit nurse. A breast cancer therapist and a psychobehavioral specialist will guide and supervise the implementation of the intervention. The entire intervention process includes a preintervention program introduction, six family meetings, and a postintervention summary. The frequency of interventions is weekly, with each meeting lasting 25–30 min. The first meeting, combined with patient follow-up time, will be an face-to-face family meeting with participating families, and the next five meetings will be online family meetings. The first follow-up visit to the hospital after surgery is usually approximately 1 week after surgery. A quiet, undisturbed environment will be chosen for family meetings. The specific time for each family meeting must be agreed upon in advance with participating families.

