One day before each meeting, meeting materials will be sent to the participants of the intervention group to inform them of the content of the meeting in advance. Two to 3 min before each meeting, there will be a review to summarize the content of the previous meeting. During the meeting, families of the intervention group will be guided to actively participate in the discussion through videos, pictures, questions, etc., to increase participation. After the meeting, participating families will be encouraged to review the content of the meeting through homework to improve the effect of the intervention. One week after the end of the intervention, participating families will be invited to assess the entire intervention process, and the assessors will collect postintervention data and give gifts to families to show appreciation for their participation. Details of the intervention plan are shown in Table 1.

**Table 1 tab1:** Outline of the coping-focused family resilience intervention program (CFFRI).

Unbreakable Belief - Know yourself and the enemy (First week after surgery)	
Theme	Understand Breast Cancer and Family Resilience
Form	Face-to-face family meeting
Target	Learn about breast cancer and how it affects families. Understand the concept and meaning of family resilience.
Content	Ask the patient and primary caregiver to share some of their questions and concerns after patients becomes ill. Explain breast cancer related knowledge to patients and their families in the form of pictures, text and videos. Combine video materials and family discussions to help family members understand the characteristics of breast cancer families and help each family member understand the changes in family roles. Explain the definition and importance of family resilience to patients and their families in a graphic and textual manner.
Homework	Review the content of this meeting through electronic meeting materials. Patients and primary caregivers share with researchers their views on breast cancer and the main effects of the disease on themselves or their families (*via* voice or text message or phone call).
Unbreakable Belief - Face with smile (Second week after surgery)	
Theme	Remain Positive
Form	Online family meeting
Target	Breast cancer treatment, life and psychology and other aspects care and precautions. Master the basic methods to relieve stress and soothe emotions.

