### Limitations

This study may have some limitations. First, there are many family meetings in the intervention program, and subjects may not be able to attend all of them due to physical or other reasons, which will lead to sample loss that may have an impact on the study results. Second, because of the nature of the study, it was not possible to blind the interventionists. Therefore, this study will arrange for independent researchers to collect and evaluate the data. Finally, while each family meeting will be held in an isolated quiet setting, some subjects may be contaminated due to subject recruitment and the first family meeting being held in the same department of the hospital. Therefore, when arranging meetings for families in the intervention group, researchers should try to choose an appropriate place and time to avoid crowd gathering and contamination between study subjects.

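### Participants are said to be blinded, but families draw their own envelope and only one arm attends family meetings; the outcomes are participant-reported and the Limitations do not say so

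*Protocol article*

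**What the plan says.** The protocol article makes the blinding claim twice.

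- Study design gives the label and its reason: "the interventionists could not be blinded in this study, so this study used a single-blind randomized controlled trial". It then says: "The experimental group will receive a family resilience intervention on the basis of usual care that will blind participants, recruiters and data collectors".
- Randomization repeats it: "Participant recruitment and assignment will be done by two independent researchers, blinding participants, recruiters and data collectors".

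The same article describes what happens to families.

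- Randomization: "Subjects will randomly draw envelopes, enter their assigned groups, and have baseline measurements taken".
- Experimental group: "The entire intervention process includes a preintervention program introduction, six family meetings, and a postintervention summary". Table 1 adds homework after each meeting, and the text has these families briefed about the program beforehand.
- Control group: "Families in the control group will receive usual care". This consists of handbooks and a WeChat group. No sham or attention control is described.
- Experimental group, one week after the intervention ends: "participating families will be invited to assess the entire intervention process, and the assessors will collect postintervention data and give gifts to families".

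The Limitations concede only that interventionists are unblinded, and offer this remedy: "Therefore, this study will arrange for independent researchers to collect and evaluate the data".

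**The concern.** A family that opens its own allocation, and then either is or is not invited to six meetings, knows its arm. The statement that participants are blinded is therefore at odds with the procedures in the same document.

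This matters because of the kind of outcome. When the person answering the questionnaire knows the arm, hopes for the program or gratitude to the team can shift the score. Blinding the person who hands out or collects the form does not touch that route. The one safeguard in the Limitations is aimed at a different route, and the exposed one is not mentioned. A reader who trusts the label would give the result more protection from expectation and reporting bias than the design provides.

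**Working it through.** **1. Claim against procedure, party by party**

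| Party | Claimed status | What the procedures show | Result |
|---|---|---|---|
| Participants | Blinded (Study design, Randomization) | They draw the envelope and join the group; one arm has a briefing, six meetings and homework, the other has usual care with no sham | Cannot hold |
| Recruiters | Blinded | Recruitment and assignment are given to two separate researchers | Can hold before allocation; nothing contradicts it |
| Data collectors | Blinded | Independent researchers are planned (Limitations), but families' evaluation of the intervention and the outcome collection fall on the same occasion (Experimental group) | Possible, at risk |
| Interventionists | Not blinded | They run the meetings | Consistent |

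Reading the participant claim as concealment until the draw does not rescue it, because Study design ties the blinding to receipt of the intervention. Reading it as blinding to the hypothesis is not supported either. No such procedure is stated, and the first meeting in Table 1 explains family resilience, the construct of the primary outcome, to the experimental families.

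**2. Who supplies the score**

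The six outcomes are the C-FRA, CSQ, SSS, FBSD, SAS and SDS. The SAS and SDS are self-rating by name. For the other four, subject report is inferred from their being questionnaire scales; the mode of administration is not stated, and Data collection speaks of investigators measuring these variables. Even if the items were read out in an interview, the answers would come from someone who knows the arm. No clinician-rated or objective outcome is described.

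**3. Illustration of size**

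The concern disputes no figure in the plan, but the illustration borrows the planned group size.

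- Sample size section: 36 per group, one-sided 0.025, power 0.9, 10% dropout. The inflation step reproduces: 36 / (1 − 0.10) = 40. The 36 cannot be reproduced, because no SD is given.
- Assumed, not in the documents: a reporting bias of b standard deviations in favour of the intervention, no true effect, and one two-group comparison.

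Error rate = Φ( b / √(2/n) − 1.960 ), with √(2/36) = 0.2357.

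| b (SD) | b / 0.2357 | minus 1.960 | One-sided error |
|---|---|---|---|
| 0 | 0 | −1.960 | 0.025 |
| 0.1 | 0.424 | −1.536 | 0.062 |
| 0.2 | 0.849 | −1.111 | 0.133 |
| 0.3 | 1.273 | −0.687 | 0.246 |

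The t distribution gives 0.241 in the last row. With all 40 per group the three non-zero rows become 0.065, 0.143 and 0.268.

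**The case against.** Participants in a behavioural trial of this kind can hardly be blinded, so the lack of blinding is not itself a fault, and no sham arm is called for. That stands. A condensed article may also leave blinding detail to a fuller protocol. That does not help here, because the problem is a positive statement, made twice, that the article's own procedures contradict.

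Several stronger readings are tempting and should not be drawn.

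- *That none of the claimed blinding exists.* Only participant blinding is shown to fail. Nothing contradicts the claim for recruiters, and independent data collectors are planned.
- *That the data collectors are unblinded.* The text joins the families' evaluation and the outcome collection in one sentence. It does not say who runs the evaluation, whether the assessors see it, or which comes first. The gift is weak evidence of arm, since Setting and recruitment and Sample size offer gifts to participants generally. This is a risk that the text does not exclude.
- *That all six outcomes are stated to be self-completed.* That is explicit only for the SAS and SDS.
- *That the bias is a known share of the design effect.* No SD is stated. Solving 36 per group backwards gives an SD of 0.29 × √18 / (1.960 + 1.282) = 0.38, or an effect of about 0.76 SD. That is inferred, and it comes from a before-after change on a different instrument (FHI, not C-FRA). A ratio of assumed bias to inferred effect would carry little information.
- *That the trial will present its results as free of reporting bias.* No section says so. What can be shown is a wrong blinding statement and an omitted limitation.

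The planned between-group analysis is repeated measures ANOVA, so the error rates above are not those of the actual test.

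**Conclusion.** The point holds for participants: the article states a blinding that its allocation and intervention procedures rule out. Because the outcomes rest on participants' answers (stated for two scales, inferred for four), independent data collectors do not remove expectation or reporting bias, and the Limitations leave this out. Blinding of data collectors is achievable, but it is at risk at the one-week assessment as now described.

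The size of any bias is unknown. Under the assumptions in the illustration, the one-sided 0.025 error rises to about 0.06 to 0.25. The conclusion does not depend on those figures; it rests on the text alone. The correction affects how firmly a positive result can be attributed to the intervention. It does not affect the arms, the outcomes or the sample size.

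**What to change.** 1. In Study design and Randomization, state that participants and interventionists are not blinded. Limit the blinding claim to recruiters, up to allocation, and to outcome-data collectors.
2. At the one-week assessment, have the independent collectors already planned, who are not told the arm, take the outcome questionnaires before any evaluation of the program. Let someone else handle that evaluation.
3. In the Limitations, add that outcomes are reported by participants who know their arm, and that independent collection does not remove the resulting bias.

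Blinding of data-entry staff or the analyst is not planned in the article and should not be claimed unless it is arranged.

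The cost is a less favourable blinding label, a fixed order of steps at the one-week assessment, and a second person for the program evaluation if the assessors were meant to run it.
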